### Study procedures

#### Study period

The inclusion period is from June 2018 until April 2020. If in April 2020 the required sample size is not reached, the patients will continue to be recruited until the minimum required number of events has been reached. Follow-up of the patients is 30 days.

#### Procedure during home visit

All patients will receive usual care. Patients will be screened for eligibility during home visits by the attending GP of the GP cooperative. Verbal informed consent will be obtained from the patient or his legal representative. The GP will be (routinely) accompanied by a chauffeur during the home visit. The chauffeurs are used to practically assist the GP during the visit. Portable monitors (Philips intelliVue MP2 or X2) will be available to record peripheral oxygen saturation, automated blood pressure, and heart- and respiratory rate by three lead electrodes on the chest.

The GP will record the assessment of the candidate predictors in a case report form. In addition, the GP will record if he/she has a gut feeling that “something is wrong” and will provide the likelihood of the presence of sepsis at inclusion on a scale from 0 to 10.

All study materials will be taken to the patient’s home in a study bag. The venous samples will be collected by either the GP or an on-call laboratory assistant or nurse within 1 h after inclusion, with a maximum of 8 h. Written informed consent will be obtained prior to the collection of the blood samples. In case the patient is referred to the hospital and the blood samples are not collected by the GP, the study bag will be transported with the patient to the ED. Subsequently, the laboratory assistant on call will visit the patient in the hospital and collect the blood samples. Three blood tubes will be collected: 10 ml for serum, 10 ml for EDTA plasma, and a 2-ml heparin tube. Lactate will be measured immediately afterwards from a single drop of blood taken from the heparin tube, using the StatStrip Xpress (Nova Biomedical) POC test. The remaining blood samples will be taken to the hospital laboratory and divided into six samples of serum and six samples of EDTA plasma. The aliquots will be temporarily stored at the local laboratory at < − 70 °C. Two samples (1 ml serum and 1 ml EDTA plasma) will be transported to the Jeroen Bosch Hospital for CRP and PCT analyses, and the remaining samples (5 × 0.5 ml serum and 5 × 0.5 ml EDTA plasma) will be stored for 15 years at < − 80 °C at the UMC Utrecht for potential future testing.

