#### Training and remuneration of personnel

Chauffeurs of the GP cooperatives will be trained in using portable monitors for vital sign measurement and other study procedures. At the GP cooperative in Ede, the chauffeurs will also be trained in the measurement of POC-lactate, as GPs will collect the venous blood samples themselves occasionally. The laboratory assistants and nurses who will be on call for the collection of the blood samples will also be trained in the POC–lactate measurement and other study procedures, including the obtaining of written informed consent. Attending GPs will be informed by an information letter by mail and hard copy at the GP cooperative. Leaflets with a summary of the study procedures will also be available.

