#### Performance of the prediction model

The performance of all three models will be determined based on their discrimination and calibration. Discrimination will be evaluated based on the area under the receiver-operator characteristic (AUROC). Calibration will be assessed by plotting observed and expected probabilities and inspecting this plot graphically. Measures of calibration will include calibration slope, calibration in the large, observed/expected (O/E) ratio, and the Brier score [25]. We will perform internal validation for all three models by using a bootstrap simulation. The resulting distribution will reflect optimism and the degree of overfitting [26].

The SIRS criteria, NEWS score, and qSOFA score will be calculated for all individuals in the TeSD-IT study. Diagnostic performance of the existing models will be determined by calculating the same measures of discrimination and calibration as described in the sections above and comparing these with the three models that were developed.

To assess the added value of the prediction models on top of usual care, other outcomes than sepsis will be considered. This is crucial for gaining insight in the net benefit of using the clinical prediction rule in daily practice. For example, when a patient is predicted as non-sepsis by the model, but the patient was referred by the GP, improvement compared to care as usual is only the case if hospital treatment was not needed according to the expert panel. To assess the added value, the proportion of reclassifications within the original contingency tables will be presented for the following outcomes: (1) the gut feeling of the visiting GP that “something is wrong”, (2) the assessment of the visiting GP for the likelihood of sepsis, and (3) the decision of the visiting GP whether or not to refer the patient to the hospital.

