The expert panels will be instructed to use the SOFA score (increase, due to infection, of ≥ 2 points from baseline) to define the primary outcome “sepsis within 72 h after inclusion”. This is consistent with the Sepsis-3 consensus definition and leads to an objective and reproducible endpoint in the absence of a gold standard. However, this approach introduces the risk of incorporation bias. Parameters included in the SOFA score are more likely to be predictive of sepsis in our model. However, the blood tests (CRP, lactate, and procalcitonin) are not included in the SOFA score, which limits the risk of incorporation bias for these tests. Furthermore, vital signs measured in the first 72 h will be used to calculate the SOFA score and not only at the time of inclusion.

Patients will receive a questionnaire at day 30 measuring EQ5D-5L. The results may be biased due to selective response and poor recall due to sepsis- or age-related cognitive impairment. Imputation of the missing answers on the questionnaires will reduce this form of bias as much as possible. Furthermore, the development of the clinical prediction rule is not affected, as the patient questionnaires will only be used for the cost-effectiveness analyses

To compare the performance of the new clinical prediction rule with usual care, not only the decision to refer the patient to the ED, but also the assessment of the GP of the likelihood of sepsis on a scale from 0 to 10 and the presence of a “gut-feeling something is wrong” will be used. We will examine if the prediction rule will outperform those assessments of the GP in order to likely improve the usual care.

Only three candidate blood tests were selected for the development of the prediction rule. Various other biomarkers have promising diagnostic and/or prognostic properties in patients with suspected sepsis [29, 30]. At the start of this study, sufficient evidence of the additional diagnostic and/or prognostic value above lactate, CRP, and PCT was lacking. However, sufficient blood samples will be stored for retrospective testing of multiple additional biomarkers.

Although to our best knowledge no clinical prediction rules for sepsis in primary care were previously developed, several sepsis screening tools were published for the ambulance setting [31]. However, none of those have adequate inclusion criteria, data collection, and clinically relevant endpoints for use in the primary care setting.

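### The usual-care comparator is GP judgement formed with study monitoring in use, and at Ede a bedside lactate could be known before referral is decided

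*Protocol article*

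**What the plan says.** Under Performance of the prediction model, the article announces the comparison: "To assess the added value of the prediction models on top of usual care, other outcomes than sepsis will be considered". It then lists three GP judgements for the reclassification tables: gut feeling, the GP's likelihood of sepsis, and "the decision of the visiting GP whether or not to refer the patient to the hospital". The Discussion repeats the aim ("To compare the performance of the new clinical prediction rule with usual care, not only the decision to refer the patient to the ED") and adds the other two judgements, closing with "We will examine if the prediction rule will outperform those assessments of the GP in order to likely improve the usual care".

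Procedure during home visit describes how the judgements arise. "The GP will record the assessment of the candidate predictors in a case report form". As a further entry the GP notes any gut feeling that something is wrong and "will provide the likelihood of the presence of sepsis at inclusion on a scale from 0 to 10". At the same visit, "Portable monitors (Philips intelliVue MP2 or X2) will be available to record peripheral oxygen saturation", together with blood pressure, heart rate and respiratory rate. Lactate is measured directly after the blood draw, from the heparin tube.

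Training and remuneration of personnel lists the monitors among the study procedures for which chauffeurs are trained. For Ede it adds that "the chauffeurs will also be trained in the measurement of POC-lactate, as GPs will collect the venous blood samples themselves occasionally".

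**The concern.** The comparison is meant to show what the rule would add to current practice. For that, the GP judgements should rest on the information a GP would have without the study. Two features of the visit may change that information.

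First, the study prompts and equips the measurement of the clinical features that the rule will later use. Second, in some Ede visits a candidate blood test may be read beside the GP while referral is still open. The rule would then be compared with a decision that already uses one of its own inputs, at one site and not at the others.

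At stake is the wording and interpretation of the added-value result, including what is concluded about avoidable referrals. A judgement made before a result was seen cannot be reconstructed afterwards unless its order was recorded.

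**Working it through.** No arithmetic applies: the article gives no figure for this comparison, and the question is what the GP knew at each judgement. The relevant statements are set side by side.

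**Step 1: vital signs.** Table 1 gives the monitor as the only listed method for heart rate, systolic blood pressure and oxygen saturation, and as one of two for respiratory rate. That is four of the nine clinical features. The training section treats monitor use as something chauffeurs must be taught, which implies, without stating it, that it was not already routine. The GP enters the predictors and the judgements on the same occasion, and the article gives no order between them. The judgements may therefore be made with the study readings known.

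**Step 2: order relative to blood.** The Methods part of the Abstract places blood sampling after the GP's clinical assessment. Procedure during home visit ties the likelihood score to inclusion and has samples taken after inclusion, once written consent is given. CRP and procalcitonin are run later from stored aliquots, so lactate is the only blood test that could be known at the visit.

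**Step 3: who draws the blood.** If the patient is referred and the GP has not drawn blood, the study bag goes to the emergency department and sampling follows there. Referral then precedes lactate. If the GP draws the blood, which the training section describes for Ede as occasional, the chauffeur can read lactate on the spot. No statement fixes whether referral has been decided by then, and none withholds the reading.

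**Step 4: result for each judgement.**

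| GP judgement | Stated time point | Study vital signs may be known | Lactate may be known |
|---|---|---|---|
| Likelihood 0 to 10 | At inclusion | Yes | Unlikely: sampling comes later |
| Gut feeling | Entered with the likelihood; no separate time given | Yes | Probably not |
| Referral | None given; not said to be entered on the form | Yes | Possible in GP-drawn cases at Ede |

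**Step 5: size.** The number of lactate-exposed referral decisions is the number of patients at Ede, times the share with GP-drawn blood, times the share of those still undecided when lactate was read. The article gives none of the three, so no count can be calculated.

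**The case against.** The strongest reply is that the article says all patients receive usual care, that the chauffeur already accompanies the GP routinely, and that the monitors are merely available. GPs may well measure most of these signs in an acutely ill adult anyway, and the article does not say which they usually measure. This stands as a limit: how far the visit departs from usual care is unknown. It does not remove the point, because Table 1 makes the monitor the standard method for several predictors and the comparator still carries the usual-care label.

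A second reply is that giving the GP and the rule the same clinical findings is a legitimate design, since it asks whether formal combination plus blood tests beats judgement. This also stands. It is the reason not to demand that judgements be written before the vital signs are seen: a GP without vital signs is not shown to be usual care either, and the rule would then hold information denied to its comparator.

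A third reply is that form layout and entry order belong to study materials not shown. That is fair for the layout. But the article itself defines the comparison as one with usual care and itself describes the procedures that bear on it.

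A reader might infer more: that lactate contaminates all three judgements, or that the rule's added value is certainly understated. The article supports neither. The order in Step 2 largely protects likelihood, and probably gut feeling. Understatement would follow only if the extra readings improve the GP's judgement, which is plausible but not established.

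**Conclusion.** The concern holds in a limited form. The three GP judgements are presented as usual care, but they are made at a visit with study-supplied monitoring and a structured predictor record. For referral alone there is a further route: in GP-drawn cases at Ede, a candidate predictor may be known before the decision.

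The lactate route is confined to one of four cooperatives and to a minority of visits there, if occasional is taken at its word. The monitoring issue applies wherever the study equipment is used. Neither effect can be quantified from the article, and the direction of any distortion is not certain.

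The conclusion assumes that monitor use was not already routine and that no unpublished study instruction withholds lactate from the GP. Only the added-value comparison is affected; the primary outcome, model development, internal validation and sample size are not.

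**What to change.** - **Recording.** Have the GP enter gut feeling, likelihood and referral intention, with a clock time, before any blood is drawn or lactate read. Alternatively, keep the lactate reading from the GP until those entries are made. Use the recorded referral intention in the reclassification tables. Do not require the entries to precede the vital-sign readings.
- **Patients already included.** The Sample size section shows that recruitment has begun. For these patients, report how often lactate was read before referral was decided, and repeat the comparison without those cases as a sensitivity analysis.
- **Wording.** Describe the comparator as GP judgement with study vital-sign measurements available, and limit the usual-care claim accordingly.

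The cost is an additional timed entry on the form, a line in the GP leaflet and the chauffeur training, and a few cases left out of a sensitivity analysis. Where order was not recorded for earlier patients, lactate exposure may have to be reported as unknown. The preferred option, recording before blood is drawn, changes nothing in patients' care.

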### Outcome measures

The primary outcome measure is sepsis within 72 h after inclusion. This will be determined by an expert panel using the Sepsis-3 criteria [1]. The operational definition of sepsis is the presence of infection and a SOFA score (Table 2) of at least two above the baseline (which can be assumed to be zero in patients not known to have preexisting organ dysfunction).

**Table 2 Tab2:** SOFA score

System	Score			
	1	2	3	4
Respiration				
PaO_2_/FiO_2_, mmHg	< 400	< 300	< 200 with respiratory support	< 100 with respiratory support
Coagulation				
Platelets, × 10^3^/μl	< 150	< 100	< 50	< 20
Liver				
Bilirubin, μmol/l	20–32	33–101	102–204	> 204
Cardiovascular				
Hypotension	MAP < 70 mmHg	Dopamine ≤ 5 or dobutamine (any dose)^a^	Dopamine 5.1–15, or epinephrine ≤ 0.1, or norepinephrine ≤ 0.1	Dopamine > 15, or epinephrine > 0.1, or norepinephrine > 0.1
Central nervous system				
Glasgow Coma Score	13–14	10–12	6–9	< 6
Renal				
Creatinine, μmol/l	110–170	171–299	300–440	> 440
Urine output, ml/day			< 500	< 200

Adapted from Vincent et al. [20]

*PaO*_*2*_ partial pressure of arterial oxygen, *FiO*_*2*_ fraction of inspired oxygen, *MAP* mean arterial pressure

^a^Adrenergic agents administered for at least 1 h (doses given in μg/kg/min)

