### Sample size

In total, 12 candidate predictors are chosen for the development of the prediction model (Table 1). Using the rule of thumb of 10 events per variable [23], we need 120 patients reaching the primary outcome “sepsis within 72 h after inclusion” in the final dataset. Prior to the start, the prevalence of sepsis based on previous research and literature was estimated to be around 12%. However, preliminary data analysis from the patients included in the study so far indicates the prevalence of sepsis in the study cohort to be around 30–40%. After the first 100 cases will be assessed by the expert panel, we will determine the final target sample size.

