#### Development of the prediction model

A multivariable penalized logistic regression model will be developed, based on the variables listed in Table 1, for predicting the primary outcome (sepsis within 72 h after inclusion). We will use a two-stepped approach entering and selecting clinical features first, and blood tests second. In both steps the selection of predictors will be based on a stepwise backward selection, using change in Akaike information criterion (AIC) for selecting the preferred model [24]. The goal is to generate an efficient model by eliminating variables that contribute little to the model’s performance, requiring only measurement of the most important variables in clinical practice.

Continuous predictors in the model will be assessed for linear relationship with the logit of the primary outcome. Transformation of the data and splines will be used if deemed appropriate based on distribution of the data.

The resulting prediction model will be the most accurate prediction model, by making use of continuous measurements of predictors and reflecting non-linear relationships by transformations or splines (optimal model). To make this model workable in daily clinical practice without electronic aids, a second model will be derived (clinical practice model) by categorising or stratifying predictors. Cutoffs for categorisation will be based on a combination of known and commonly used thresholds in clinical practice and optimal thresholds based on the data. This model simplification is likely to induce a performance drop with regard to the full model, which will be assessed during the analysis.

The above procedures will result in the following three models: (1) optimal model with clinical features only, (2) optimal model with clinical features and blood tests, (3) simplified model (with clinical features and blood tests).

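### The GP rates sepsis present at inclusion while the rule targets sepsis within 72 h; judged against the 72 h outcome, that one comparison can favour the rule

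*Protocol article*

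**What the plan says.** Under Procedure during home visit, the GP fills in a case report form and "will provide the likelihood of the presence of sepsis at inclusion on a scale from 0 to 10". Under Outcome measures, "The primary outcome measure is sepsis within 72 h after inclusion", as decided by an expert panel. No panel judgement of sepsis at the time of the visit is described. Development of the prediction model takes the 72 h label as the target of the regression. The Discussion adds that "vital signs measured in the first 72 h will be used to calculate the SOFA score and not only at the time of inclusion".

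The GP's score returns under Performance of the prediction model, where "the assessment of the visiting GP for the likelihood of sepsis" is the second of three items for which reclassification is shown. The other two are the gut feeling that something is wrong and the actual referral decision. The Discussion states the purpose: "We will examine if the prediction rule will outperform those assessments of the GP in order to likely improve the usual care". The difference in time horizon is not mentioned anywhere.

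**The concern.** On a plain reading, the GP is asked about now, and the rule is trained on the next three days. Take a patient who is not septic at the visit but meets the criterion on day 2. A GP who answers the question as put should rate this patient low. Against the 72 h label that answer counts against the GP, although it was correct. The rule is fitted with the same patient labelled as a case.

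At stake is the statement that the rule outperforms the GP's own estimate of sepsis. Part of any advantage could come from the difference in question. Bootstrap validation would not remove that part, because it corrects for optimism in the model and not for a difference in target.

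**Working it through.** **1. The plan's own figures (background only).** Sample size: 12 candidate predictors × 10 events = 120, matching "we need 120 patients reaching the primary outcome". The Discussion gives about 350 patients at an outcome rate of 0.35; 120 / 0.35 = 343, within about 2%. The alternative calculation based on rMPSE was not repeated, because its formula is not in the article. The 120 events serve below only to turn shares into counts.

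**2. The horizons side by side.**

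| Element | Section | Horizon |
|---|---|---|
| GP's 0–10 sepsis score | Procedure during home visit | At inclusion (plain reading) |
| Panel classification | Outcome measures | Within 72 h |
| Target of the models | Development of the prediction model | Within 72 h |
| GP's score as comparator | Performance of the prediction model | No reference standard named |

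**3. Effect on the GP's apparent accuracy.** Inputs, none of them given in the article:
- f: share of 72 h cases not yet septic at inclusion; assumed 0 to 30%.
- Se, Sp: accuracy of the dichotomised GP score against sepsis at inclusion; assumed 0.80 each.
- q: proportion of late cases that the GP rates positive.

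Apparent sensitivity against the 72 h label = (1 − f) × Se + f × q, so the loss is f × (Se − q). It cannot be negative as long as late cases are rated positive no more often than cases already present. If late cases are rated like non-cases, q = 1 − Sp and the loss is f × (Se + Sp − 1). Specificity then stays at Sp. The AUC of a single cut-off is (apparent sensitivity + Sp) / 2.

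| f | Late cases of 120 | Apparent Se | Loss (points) | Single-cut AUC | Apparent Se, perfect rater |
|---|---|---|---|---|---|
| 0% | 0 | 0.80 | 0 | 0.80 | 1.00 |
| 5% | 6 | 0.77 | 3 | 0.785 | 0.95 |
| 10% | 12 | 0.74 | 6 | 0.77 | 0.90 |
| 20% | 24 | 0.68 | 12 | 0.74 | 0.80 |
| 30% | 36 | 0.62 | 18 | 0.71 | 0.70 |

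Example: at f = 10%, 0.90 × 0.80 + 0.10 × 0.20 = 0.74.

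**4. Milder case.** If GPs already sense deterioration and rate half of the late cases positive (q = 0.50, assumed), the loss is f × 0.30: 3 points at f = 10% and 6 at f = 20%. If they rate late cases like present ones (q = 0.80), it is zero.

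**The case against.** Five points can be made against this.

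- **Wording.** The article paraphrases a form that is not shown, and the phrase about inclusion may say when the rating is given. This is possible. Even so, the plain reading is presence at inclusion, and a phrase open to both readings lets GPs answer different questions.
- **Reference standard.** Performance of the prediction model names none for the GP's score. It says that outcomes other than sepsis will be considered, and its worked example turns on the panel's view of the need for hospital treatment. This stands: judging the score against 72 h sepsis is an inference from its being the only sepsis outcome defined. A separate analysis plan may name the reference, but it cannot change what the GP was asked. The outcome on hospital need does not bring the two sepsis horizons together.
- **Scope.** Only one of three GP comparators is affected. This stands in full. Model development, internal validation and the comparison with SIRS, NEWS and qSOFA are also unaffected.
- **Size.** f, Se and Sp are assumptions, the score is graded, and no cut-off is stated. This stands.
- **Timing of onset.** Platelets, bilirubin and creatinine come from hospital records over 72 h (Data extraction), so dates show first measurement and not onset. This also stands. Some apparently late cases were probably septic at the visit, and the fix has to allow for that.

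A reader might infer that every later-onset case becomes a GP miss while the rule is credited with it. The documents do not support that. A late case is a miss only if the GP rated it low. The rule's predictors are recorded at the visit, with blood samples within at most 8 h, so it may miss the same patient.

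**Conclusion.** The point holds in limited form. If the GP's likelihood score is judged against the 72 h outcome, the mismatch can only lower, or leave unchanged, the apparent accuracy of a better-than-chance GP rating, provided that late cases are rated no higher than cases already present. The rule carries no such penalty from the question asked, so the comparison can tilt its way.

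The size cannot be computed from the protocol. Under the assumptions in the table, the GP loses 6 points of sensitivity at f = 10% and 12 at f = 20%. The loss cannot exceed f, the value for a perfect rater, and is about zero if nearly all cases are septic at the visit. A reader might go on to infer that the whole comparison with usual care is biased, or that any advantage of the rule is an artefact. Neither follows, because two of the three GP comparators are not tied to sepsis at inclusion and f may be small.

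**What to change.** 1. **Patients still to be enrolled.** Word the GP item as the likelihood that sepsis is present now or will be present within 72 h, on the same 0–10 scale. Report ratings under the two wordings separately. Cost: one line on the form. Downside: since recruitment is under way, the comparator splits into two smaller sets.
2. **Patients rated under the present wording.** Have the panel also record whether sepsis was probably already present at inclusion, arose later, or cannot be timed. The third option is needed because first measurement is not onset. Report the GP's score and the rule against both labels as a sensitivity analysis. Cost: one extra item on the panel form, using records that the panel already receives. The timing will be least certain for patients never seen in hospital.
3. **Reporting.** Name the reference standard for the GP's score. Rest any statement that the rule outperforms the GP's estimate of sepsis on the comparison with a shared horizon. If neither change is feasible, state the mismatch as a limitation that favours the rule; that costs one sentence.
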